#### Secondary outcome measures

##### Thromboembolic complications

We will track the incidence of transient ischemic attack or ischemic stroke during the study period, in addition to the eventual difference between both study populations.

##### Death

We will keep track of all-cause mortality during the study period, as well as the difference in mortality between control and intervention populations.

##### Compliance

We will keep track of patient compliance during the study period (e.g., minimum number of measurements with FibriCheck®).

### Participant timeline {13}

The study will be conducted over the course of 12 months in general practices in the Flanders region of Belgium, planned to run from January 2022 to December 2022.

Allocation of control and intervention practices is planned to start around November 2021. Eligible participants will be followed in their usual primary care practice, and are recruited by the participating physician when they visit for whatever reason. They will be provided an information leaflet, a consent form, and 1 week decision time.

Participants will be followed for a total of 4 weeks. Measurements and other data will be collected and interpreted at the end of this period. After the total study period of 12 months, the resulting data will be analyzed.

A schematic overview of the timeline can be found in Table 1. A visual representation of the study flow can be found in Fig. 1.

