### Trial design {8}

This study will be a cluster randomized trial: primary care practices will be randomized and divided into a control and intervention group. Allocation of control and intervention groups will be done by simple balanced randomization (1:1).

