### Concealment mechanism {16b}

Researcher B will prepare sealed, opaque envelopes containing a paper that assigns a specific practice number to a study group, based on this randomly generated number sequence. The process of the envelope preparation up until sealing and storage in a locked compartment will be videotaped by researcher B, who will thereafter be excluded from every other aspect of the trial. Allocation papers should never be visible, only the envelopes and the numbers on them. The video will be stored on an external device, which will be put in the locked compartment.

After practice enrolment, researcher A will access the locked compartment with the envelopes and review the accompanying video to ensure proper envelope preparation. Without opening or tampering with the letters, researcher A will write the appropriate mailing address on the respective envelope, based on their numbered list of practices. The envelopes will only be opened by the practices if they have an unbroken seal. This protocol is adapted from Radford et al. [35].

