### Implementation {16c}

All Flemish primary care practices in the INTEGO network conforming to the inclusion criteria will be contacted for inclusion in the study. Then, they will be randomly subdivided into intervention and control practices by the method described above. There will be an equal amount of intervention and control practices. In every practice, patients will be selected according to the previously defined in- and exclusion criteria, mentioned above. Later, high-risk patients in the intervention groups will be identified using the CHARGE-AF score, and will be prescribed the FibriCheck® app. High risk is defined as a 5-year risk of AF of at least 10% according to this score. The GPs in the intervention practices will explain the study outline to these patients and instruct them how to use the app, after which the study period begins for those patients.

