## Assignment of interventions: Blinding

### Who will be blinded {17a}

Due to the nature of the study, it is not possible to blind at the practice level. Physicians will always be aware to which group they belong, as will the patients.

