## Statistical methods

### Statistical methods for primary and secondary outcomes {20a}

We will analyze our data on an intention-to-screen basis, evaluating the outcomes on the practice (cluster) level. There will be no subgroup analyses.

The intention-to-screen analysis means we will include all participants of both the control and intervention groups in the final analysis, regardless of whether they did receive the stated screening intervention or dropped out before they could do so. This ensures that no bias is introduced by looking at the data on the practice level, for example by erroneously overestimating the effect of the intervention (screening with FibriCheck® on top of standard screening). This approach is valid as long as the studied population is appropriately randomized [36].

We will analyze the results on the cluster level, as the study is also randomized at the cluster level. Statistical efficiency should be sufficient with the cluster sizes being equal, as outlined above. As the unit of inference will be the cluster, and not the participant, we will apply standard *t* tests with inverse-variance weighting [37]. Given the fact that we have two independent study populations, we will use the paired (independent samples) *t* test. Because the observations within each cluster will likely be correlated, it is essential to account for this correlation, by choosing an appropriate method of analysis. The small number of clusters in this study could lead to an inflation of the type I error when applying individual level analyses. Inverse-variance weighting is one cluster-level strategy to reduce the type I error while maintaining sufficient statistical power [37].

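### Allocation is concealed from practices but not at patient entry, so who is enrolled can differ by arm, in either direction, and intention-to-screen does not remove that

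*Protocol article*

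**What the plan says.** - **Unit of randomisation.** Under Trial design {8}, "primary care practices will be randomized and divided into a control and intervention group".
- **Concealment.** Concealment mechanism {16b} describes opaque sealed envelopes, prepared on video and addressed without being opened. It ends at the practice: "The envelopes will only be opened by the practices if they have an unbroken seal".
- **Order of events.** Participant timeline {13} states "Allocation of control and intervention practices is planned to start around November 2021", with the study "planned to run from January 2022 to December 2022". Implementation {16c} divides the practices and then continues: "In every practice, patients will be selected according to the previously defined in- and exclusion criteria, mentioned above".
- **Who recruits.** Patients "are recruited by the participating physician when they visit for whatever reason" (Participant timeline {13}). The participating physician gives out the leaflet and consent form in both arms (section {26a}), and control patients must also sign (Eligibility criteria {10}).
- **Blinding.** "Physicians will always be aware to which group they belong, as will the patients" (section {17a}).
- **Analysis.** Section {20a} includes all participants of both groups on an intention-to-screen basis, with a weighted t test on practices, and says of intention-to-screen: "This approach is valid as long as the studied population is appropriately randomized". Section {20b} rules out any additional analysis.

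**The concern.** In a cluster trial, concealing which practice goes to which arm protects the set of practices. It does not protect the set of patients if they are found and consented after the practice knows its arm. Here each patient's arm is certain before the patient is approached.

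Two routes to differential entry follow from the text. The recruiter may offer the study to different patients when there is an app to offer than when there is only a consent form. Patients may also accept for different reasons in the two arms.

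The primary outcome is newly detected AF among those enrolled. If the enrolled groups differ in undetected AF, that difference is added to, or subtracted from, any effect of the app. A test on 22 practice results cannot tell the two apart.

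**Working it through.** **1. Does intention-to-screen cover it?** Section {20a} makes validity depend on the studied population being properly randomised. What is randomised is the practice. The analysed participants are those who consented afterwards with the arm known. Intention-to-screen keeps people in once they have entered; it does not govern who enters. The protocol's own condition is therefore not secured at patient level.

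**2. What would show imbalance?** Table 2 (section {18a}) collects age, sex, body mass index, blood pressure, heart rate, smoking, antihypertensive use, diabetes, heart failure and myocardial infarction for both groups. It lists neither symptoms nor an irregular pulse. Section {20a} states no adjustment for any of these.

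**3. The plan's own sample size.** Inputs from Sample size {14}: 13.65 per 1000, power 0.80, two-sided α 0.05, ICC 0.0027, 400 per practice, 15% loss. From Outcomes {12}: a 2-fold increase, so 27.3 per 1000.

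- n = [1.960·√(2·0.020475·0.979525) + 0.8416·√(0.01365·0.98635 + 0.0273·0.9727)]² / 0.01365² ≈ 1,689. With the continuity correction it is 1,833 (stated 1,835).
- Design effect: 1 + 0.0027 × 399 = 2.077. Then 1,835 × 2.077 = 3,811 per arm, and 2 × 3,811 × 1.15 = 8,765.
- Taking 24.57 per 1000 as the intervention rate gives 2,467 (2,647 corrected). Adding it to baseline gives 656 (735). Only the 2-fold effect reproduces 1,835.

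A selection difference as large as the effect that reproduces the stated size is therefore 27.3/13.65 = 2-fold.

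**4. Illustration with no app effect.** Assumption: enrolled intervention patients have f times the underlying rate of enrolled controls. The documents give no value for f. There are 11 practices per arm and 3,811/11 ≈ 346 analysed patients per practice. The variance of a practice proportion is p(1−p)(1 + 0.0027 × 345)/346.

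- f = 1.2: SE = √[(7.516 + 8.994)×10⁻⁵/11] = 0.003874; noncentrality 0.00273/0.003874 = 0.70. On 20 df the chance of a significant result favouring the app is 9.9%.
- f = 1.5: SE = √[(7.516 + 11.196)×10⁻⁵/11] = 0.004124; noncentrality 0.006825/0.004124 = 1.65; chance 35.0%.

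These use the annual rate per patient. Outcomes {12} measures detection after four weeks. Prorating (an assumption) gives 13.65 × 4/52 = 1.05 per 1000. With 11 × 346 = 3,806 control patients that is about 4 cases, against about 52 at the annual rate. A beta-binomial simulation with an unweighted t test and 20,000 trials per scenario gives these chances of a significant result favouring the app (nominal 2.5%):

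| f | 13.65/1000 per patient | 1.05/1000 per patient |
|---|---|---|
| 1.1 | 5.1% | 2.2% |
| 1.2 | 9.8% | 2.7% |
| 1.3 | 16.6% | 3.5% |
| 1.5 | 35.8% | 4.7% |

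The low right-hand column reflects how few events there are. The detection-rate ratio itself is distorted by the factor f in both columns.

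**The case against.** Several stronger readings are tempting, and the documents do not support them.

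- **That GPs are free to choose whom to approach.** Intervention description {11a} has software compute CHARGE-AF from the record, flags all high-risk patients, and says these are then informed about the study. Palpitations and pulse irregularity are not variables in that score. This narrows discretion in the intervention arm. It does not settle who is approached at a visit or who accepts, and no such step is stated for controls.
- **That there is much room to pick.** Study setting {9} implies about 400,000/100 = 4,000 patients per office. If 15–25% are 65 or older (assumption), that is 600–1,000 before exclusions, against a target of 400. Room is limited but not absent.
- **That the bias favours the app.** App volunteers could be healthier, which would bias towards no effect. A GP who palpates and diagnoses a patient without enrolling them can be in either arm, since both screen opportunistically.
- **That the plan could reveal nothing.** Table 2 would show imbalance on most CHARGE-AF predictors. What stands is that unmeasured differences stay hidden and measured ones are not adjusted for.
- **That the false-positive risk is about 36%.** That figure needs the annual rate to apply to each patient and an assumed f of 1.5. The simulated test was also unweighted, whereas the plan specifies inverse-variance weighting.
- **That a 1.8-fold difference would match the planned effect.** Reading 24.57 per 1000 as a rate does not reproduce 1,835; 2-fold does.

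None of this removes the sequence: practice allocation known first, patient entry second, recruiter and patient unblinded.

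**Conclusion.** The point holds as a risk, not as a demonstrated bias. The protocol conceals practice allocation well and leaves patient entry open to arm-aware approach and consent in both arms. Neither intention-to-screen nor an unadjusted t test corrects what may follow, and a later analysis plan cannot change who was enrolled.

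Direction and size are unknown. Under an assumed 1.2- to 1.5-fold difference in underlying rate and no app effect, the chance of a significant result favouring the app runs from about 10–35% (annual rate per patient) down to about 3–5% (rate prorated to four weeks). The true four-week yield may lie between. These figures rest on 11 practices per arm, 346 analysed patients each, ICC 0.0027 and an unweighted test.

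**What to change.** 1. Before any envelope is posted, run one identical INTEGO query in all 22 practices: age 65 or older, no AF, no anticoagulant, no pacemaker, no exclusion diagnosis code, and a CHARGE-AF 5-year risk of at least 10%, applied in both arms from data then in the record. Freeze the list. The threshold belongs in the query because the objective concerns high-risk patients.
2. Enrol only listed patients. Keep visit-based recruitment, so that the comparator stays opportunistic, but have GPs in both arms offer the study to every listed patient who attends.
3. Report listed, attending, approached and consenting numbers, with baseline risk, by arm.
4. Amend section {20b} to allow one supporting cluster-level comparison of coded new AF among all listed patients, subject to ethics approval for using pseudonymised data of non-consenters.

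**Cost.** One query per practice and wording changes in sections {13}, {16c} and {20b}. Recruitment had not started (Trial status). Patients whose score data are missing at the freeze date cannot be enrolled, whereas section {11a} now lets GPs complete the data at the first consultation. The Discussion notes that some software packages cannot search every score parameter, so the query depends on the INTEGO extraction. List sizes should be checked against the 400 per practice. The all-listed analysis dilutes the effect, so it is supporting only. Acceptance can still differ by arm, since consent follows unblinding; items 3 and 4 make that visible but do not prevent it.

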**Table 1 Tab1:**
[figure not shown]
SPIRIT figure – Schedule of enrolment, interventions, and assessments.

**Fig. 1 Fig1:**
[figure not shown]
Visual representation of the study flow. EMR, electronic medical record

### Sample size {14}

The calculation hereafter is similar to that of an earlier paper, comparable to ours [34]. We used an online calculator, which can be found at http://www.sample-size.net/sample-size-proportions.

The sample size calculation was performed for the primary outcome (AF detection rate at practice level). In the INTEGO database, we found a baseline AF incidence of 13.65/1000 patients, 65 years or older, in 2015. As stated above, we estimated a realistic absolute increase of 24.57 AF cases per 1000 patients per year in the intervention group. The power calculation, with a power of 0.80 and an α of 0.05, for a two-sided two-sample *t* test, with the incidence of AF per 1000 patients per year as the outcome variable, led to a sample size of 1835 patients in each arm of the study.

As we will view the results on the practice level, the number of practices needs to be determined, considering the intra-cluster correlation coefficient (ICC). A similar study found an ICC of 0.0027 (18). As we plan to let this study run for 12 months, we wish to include 400 patients (= *m*) per practice/physician. Calculating the variance inflation factor (1 + ICC (*m* – 1)) leads us to a value of 2.077. To accommodate the expected variance, we will have to include 1835 × 2.077, or 3811 patients per arm. We will assume a loss to follow-up of 15% [32]. This brings us to a total study population of 8765 patients, or approximately 11 control and 11 intervention practices.

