### Outcomes {12}

#### Primary outcome measures

##### Detection rate of AF in patients 65 years and older

The detection rate of AF in both the control and intervention group will be calculated after 4 weeks. A significant difference in both groups will be noted. Compared with previous studies of similar design [32–34], we will realistically assume a 2-fold increase in the detection rate of AF in the intervention group to be significant.

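### The 24.57 per 1000 "we estimated a realistic absolute increase of 24.57 AF cases per 1000 patients per year in the intervention group" wording conflicts with the 2-fold assumption and does not give 1835 per arm; 1835 fits a doubling to 27.30 per 1000

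*Protocol article*

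**What the plan says.** In the protocol article, the section on Outcomes {12} sets the effect for the AF detection rate: "we will realistically assume a 2-fold increase in the detection rate of AF in the intervention group to be significant".

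Sample size {14} gives the control rate: "we found a baseline AF incidence of 13.65/1000 patients, 65 years or older, in 2015". It then refers back to an earlier statement and continues: "we estimated a realistic absolute increase of 24.57 AF cases per 1000 patients per year in the intervention group". The calculation uses a proportions calculator, is specified "with a power of 0.80 and an α of 0.05" and "for a two-sided two-sample", and "led to a sample size of 1835 patients in each arm of the study".

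The section next applies an ICC of 0.0027 with 400 patients per practice, giving a variance inflation factor of 2.077 and 3811 patients per arm. It adds 15% for loss to follow-up: "This brings us to a total study population of 8765 patients, or approximately 11 control and 11 intervention practices".

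**The concern.** The effect size is the input that fixes the trial's size and the meaning of its power. Here the sample size sentence gives one effect and the statement it refers back to gives another. The number of patients derived from them agrees with only one, and it is not the one written beside it.

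A reader who takes the sample size sentence at face value would think that the trial was built to detect nearly a tripling. A reader who takes 24.57 as the expected rate in the intervention arm would think that the trial has 80% power for an effect for which it has less. A null result would be interpreted differently under each.

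**Working it through.** **Inputs.** Control rate p1 = 0.01365 (Sample size {14}). Two-sided alpha 0.05 and power 0.80 (same section), so z = 1.960 and 0.8416. Equal allocation (Trial design {8}). I use the two-proportion formula because the section names a proportions calculator.

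**Candidate intervention-arm rates p2**
- 2-fold, as in Outcomes {12}: 2 × 13.65 = 27.30 per 1000, an increase of 13.65.
- 24.57 as an increase, as written: 13.65 + 24.57 = 38.22 per 1000, and 38.22/13.65 = 2.8-fold.
- 24.57 as a level: 24.57/13.65 = 1.8-fold, an increase of 10.92. The article does not state this reading; it is considered because the ratio is exact.

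**Formula per arm**, with d = p2 − p1 and p̄ = (p1 + p2)/2:

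n = [1.960 √(2p̄(1 − p̄)) + 0.8416 √(p1(1 − p1) + p2(1 − p2))]² / d²

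Continuity-corrected: n′ = (n/4)[1 + √(1 + 4/(n d))]²

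**Reproducing 1835.** For 13.65 against 27.30, p̄ = 0.020475 and d = 0.01365. Then n = (0.3925 + 0.1684)²/0.01365² = 1689, and n′ = 1832, within 3 of the stated figure.

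| Reading | p2 per 1000 | n | n′ |
|---|---|---|---|
| 2-fold | 27.30 | 1689 | 1832 |
| 24.57 as an increase | 38.22 | 656 | 735 |
| 24.57 as a level | 24.57 | 2466 | 2646 |

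Unpooled-variance, Poisson and arcsine versions do not bring either reading of 24.57 to 1835 (for example, unpooled 653 and 2464).

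**Reproducing the later steps.** 1 + 0.0027 × 399 = 2.077. 1835 × 2.077 = 3811. 2 × 3811 × 1.15 = 8765. All match the article.

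**Power of the planned trial.** I take 11 practices per arm, ICC 0.0027, and a cluster-level t test on 20 degrees of freedom (critical value 2.086). The standard error is √{[p1(1 − p1) + p2(1 − p2)] × DE/(11m)}, where m is the number analysed per practice and DE = 1 + 0.0027(m − 1). With 15% loss, m = 0.85 × 400 = 340 and DE = 1.915; without loss, m = 400 and DE = 2.077.

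| Intervention-arm rate per 1000 | m = 340 | m = 400 |
|---|---|---|
| 27.30 | 82% | 85% |
| 24.57 | 66% | 70% |
| 38.22 | over 99% | over 99% |

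**Loss step.** To retain 3811 per arm after 15% loss, one divides by 0.85: 2 × 3811/0.85 = 8967, which is 202 more than 8765. But 3811 assumes 400 analysed per practice. If 15% are lost, 340 remain and the design effect falls to 1.915. The need is then 1835 × 1.915 ≈ 3515 completers per arm, or 2 × 3515/0.85 ≈ 8270 enrolled. Eleven practices with 340 completers supply 3740 per arm, more than 3515.

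**The case against.** The strongest reply is that this is a wording error in a trial of adequate size. The sample size sentence refers back to an earlier effect, the only earlier effect is the doubling, and 1835 fits the doubling almost exactly. On that reading power is above 80% and no patient number changes. This reply largely stands, and the preferred correction follows it. It does not rescue the sentence: 24.57 is not the increase under a doubling, and no reading of it yields 1835.

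A reader might go further and infer that the trial is underpowered, because 24.57 is exactly 1.8 × 13.65 and so looks like an intervention-arm level. The article never mentions a 1.8-fold rise and never calls 24.57 a level, so this remains a scenario. Only in that scenario does power fall to 66–70%. The plan's own chain would then ask for 2646 × 2.077 × 2 × 1.15 ≈ 12,640 patients.

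A reader might also infer a shortfall from the loss step, because 85% of 8765 leaves about 3725 per arm, below 3811. That sets patients counted after loss against a requirement computed at the cluster size before loss. Compared like with like, 3725 exceeds 3515. Raising the target to 8967 is not needed either, and would exceed the 22 × 400 = 8800 patients that the planned practices supply.

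**Conclusion.** The point holds as an internal contradiction in the effect size. The article states two incompatible effects, a doubling (to 27.30 per 1000) and an absolute increase of 24.57 (to 38.22 per 1000), and its 1835 per arm agrees only with the first. The sentence is wrong as written and should be corrected, because the primary power statement rests on it.

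The size of the problem depends on what the sponsor meant. Under a doubling the design stands, with about 82–85% power. If 24.57 was the expected intervention-arm rate, the 80% claim is wrong and power is about 66–70%. The documents favour the doubling but do not settle the matter.

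These power figures assume equal practices, an ICC of 0.0027 and the annual incidence on which the plan bases its calculation. They do not address the 4-week assessment of the outcome. The loss step is a genuine slip with no material consequence.

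**What to change.** State one effect in Sample size {14}, identical to the one in Outcomes {12}.

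- **Preferred, because it agrees with the 2-fold assumption and with 1835:** give the effect as an absolute increase of 13.65 per 1000, from 13.65 to 27.30 (2-fold), delete 24.57, and note that the calculation uses a continuity correction.
- **If the sponsor confirms that 24.57 per 1000 was the intervention-arm rate:** call it a level, give the increase as 10.92 per 1000 (1.8-fold), align Outcomes {12}, and restate power as about 66–70% with 22 practices.

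In the same paragraph, redo the loss step at the cluster size after loss: 340 per practice, design effect 1.915, about 3515 completers per arm and about 8270 enrolled. Say that 8765 patients in 22 practices covers this for n = 1835.

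The cost is one corrected paragraph. Neither restatement needs additional patients or practices.

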## Discussion

To our knowledge, this will be the first study to evaluate the influence of a stand-alone smartphone application on the detection rate of AF compared to a control group. There are certain indispensable elements on which the study will hinge. Certain issues can be expected here.

Most importantly, the availability of correctly coded data is essential for the study to be conducted. Physicians must code diligently and completely. Without coded data and diagnoses, this study will be difficult to perform on a large basis. In the INTEGO database, it is possible to identify practices who code well, based on frequency and amount of coded diagnoses per consultation.

To screen high-risk patients, we will use the sufficiently validated CHARGE-AF score. Certain EMD software packages, however, do not allow custom searches based on every parameter in this score. Ideally, a tool could be developed that automatically calculates the CHARGE-AF score across platforms for every individual patient and notifies the physician if a patient needs to be screened.

The 4-week screening period was determined from other studies [34, 38]. A similar study found an increase in the cumulative diagnostic yield for AF from 0.4% for a single measurement to 1.4% for a week-long screening [38]. Based on these results, we believe that a screening period of 4 weeks will provide sufficient diagnostic yield.

There are certain limitations to this study as well. For the data to be correctly sent to the cloud, patients must have a working internet connection. Also, patient compliance is important. This will have an impact on the detection rate of AF that we will find in both study groups.

A recently published study of similar design found no increased diagnostic yield for AF when comparing opportunistic screening with regular care [39]. This study differs from ours in some important aspects, most notably the fact that opportunistic screening was limited to GP practices, whereas in our study the screening is extended with the use of a smartphone application.

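### The sample size rests on annual AF incidence, but the primary outcome is detection over 4 weeks, so the stated 80% power for a doubling does not apply to that outcome

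*Protocol article*

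**What the plan says.** The first primary outcome in Outcomes {12} has a 4-week window: "The detection rate of AF in both the control and intervention group will be calculated after 4 weeks". Participant timeline {13} agrees: "Participants will be followed for a total of 4 weeks". Section {20c} leaves out of the results anyone who does not complete the 4 weeks. The 12 months is the calendar length of the study: "After the total study period of 12 months, the resulting data will be analyzed".

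The target effect is in Outcomes {12}: "we will realistically assume a 2-fold increase in the detection rate of AF in the intervention group to be significant".

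Sample size {14} states that the calculation is for the primary outcome. Its control rate is annual: "we found a baseline AF incidence of 13.65/1000 patients, 65 years or older, in 2015". The effect is worded differently from Outcomes {12}: "we estimated a realistic absolute increase of 24.57 AF cases per 1000 patients per year in the intervention group". The calculation is described as a two-sided two-sample t test at 80% power and 5% alpha, "with the incidence of AF per 1000 patients per year as the outcome variable". It gives 1835 patients per arm. With an ICC of 0.0027, 400 patients per practice and 15% loss, this becomes 8765 patients in about 11 + 11 practices.

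**The concern.** Each patient contributes 4 weeks, yet the planning rate is what usual care finds in a year. The 12 months enters the sample size section only as the reason for expecting 400 patients per practice. No sentence converts the annual rate, and none argues that 4 weeks of opportunistic screening would find a full year of cases.

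This is the only power statement for the first-listed primary outcome. If the 4-week control rate is well below 13.65 per 1000, the trial expects far fewer events than planned. A reader relying on the stated 80% would then take a null result as evidence against a doubling when it is not.

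**Working it through.** **1. Reproduce the plan's figure.** Inputs: p1 = 0.01365; p2 = 2 × 0.01365 = 0.0273; two-sided alpha 0.05; power 0.80. The mean proportion is 0.020475.

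n = [1.960 √(2 × 0.020475 × 0.979525) + 0.842 √(0.01365 × 0.98635 + 0.0273 × 0.9727)]² / 0.01365² = 1689.

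Continuity correction: (1689/4) × [1 + √(1 + 4/(1689 × 0.01365))]² = 1832, against 1835 stated.

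The other readings of the effect do not give 1835:
- 24.57 per 1000 as the intervention rate: 2467, or 2647 with correction.
- 24.57 per 1000 added to the control rate (38.22 per 1000): 656, or 735 with correction.

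The later steps also reproduce: 1 + 0.0027 × 399 = 2.077; 1835 × 2.077 = 3811; 2 × 3811 × 1.15 = 8765. So the size comes from a doubling of full-year incidence, with no conversion.

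**2. Put the rate on the 4-week base.** Assuming even accrual over the year, 13.65 × 4/52 = 1.05 per 1000. This is an assumption, because the protocol states no 4-week control rate. Higher rates are therefore shown too.

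**3. Power for a doubling at the planned size.** Completers per practice: 400 × 0.85 = 340. Per arm: 11 × 340 = 3740. Design effect: 1 + 0.0027 × 339 = 1.915. Degrees of freedom: 22 − 2 = 20.

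Standard error = √{[p1(1 − p1) + p2(1 − p2)] × 1.915/3740}. Power comes from the non-central t distribution with non-centrality (p2 − p1)/standard error.

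At 1.05 against 2.10 per 1000, the standard error is 0.00127 and the non-centrality is 0.00105/0.00127 = 0.83. Expected cases are about 4 against 8.

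| 4-week control rate per 1000 | Power for a doubling |
|---|---|
| 1.05 (pro rata) | 12% |
| 2 | 19% |
| 4 | 34% |
| 6 | 47% |
| 8 | 59% |
| 10 | 69% |
| 13.65 (a full year of cases) | 82% |

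A simulated cluster-level t test (11 + 11 practices of 346 patients, beta-binomial) also gives about 12% at the pro-rata rate. Setting the ICC to 0 raises the formula figure there only to 19%.

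**4. Effect needed for 80% power at this size.**

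| Control rate per 1000 | Intervention rate per 1000 | Fold increase |
|---|---|---|
| 1.05 | 7.0 | 6.7 |
| 2 | 8.9 | 4.5 |
| 4 | 12.5 | 3.1 |

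**5. The second stated effect.** 24.57/13.65 = 1.8, so as an intervention rate it is a 1.8-fold increase. As an added increase, (13.65 + 24.57)/13.65 = 2.8-fold. Neither is a doubling. At 2.8-fold, power is 24% at 1.05 per 1000 and 69% at 4 per 1000.

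**The case against.** **The pro-rata rate may be too low.** Patients are recruited at a GP visit and known AF is excluded, so opportunistic screening may find existing undiagnosed AF at enrolment. The Background cites silent AF in 2.4% of adults and expects persistent AF rarely to be missed. This stands, and 12% is the low end of the range. A reader might take the cited yields, "from 0.4% for a single measurement to 1.4% for a week-long screening", as capping the control rate at 4 per 1000. They do not: they come from one other study and bound nothing in this population. The table therefore runs higher. Even so, a doubling reaches 80% power only when 4 weeks yields about a full year of cases.

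**The app may do much better than double detection.** This also stands. The Discussion cites a fourfold increase in a trial with another device and twice-weekly measurement; fourfold at a control rate of 4 per 1000 gives 95% power. If the app found 14 per 1000, power would be 99% at a control rate of 1.05 and 88% at 4. But those are different planning assumptions from the one written down.

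**The intended outcome may be 12-month detection per practice.** The Abstract places the comparison at the end of the study, and INTEGO collects practice data automatically. On that reading the calculation fits a doubling. Outcomes {12} and Participant timeline {13} would then be the text to change, and the two parts still disagree as written.

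**Conclusion.** The concern holds as a mismatch of time base. The sample size is arithmetically sound for a doubling of annual incidence, but the outcome it is said to serve is measured over 4 weeks. The stated 80% power for a doubling fails at any 4-week control rate clearly below 13.65 per 1000; across 1.05 to 10 per 1000 it is 12% to 69%. These figures assume 340 completers in each of 22 practices, the protocol's ICC and a t test with 20 df.

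A reader might infer that the trial is underpowered, or can succeed only if the app finds many times the control yield. The protocol does not support either. About 6.7-fold is needed at the pro-rata rate but only 3.1-fold at 4 per 1000, and the true control rate is not stated. What is established is that the justification for the size does not match the outcome.

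**What to change.** Align the outcome window and the calculation, in one of two ways:

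- **Keep 4 weeks.** Redo Sample size {14} with an explicit assumed 4-week yield in each arm, a range of control rates and the resulting power. Withdraw the claim of 80% power for a doubling.
- **Use 12 months.** If annual practice-level detection is what was meant, define the primary outcome over 12 months in Outcomes {12} and Participant timeline {13}, and bring the 4-week completion rule in {20c} into line.

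In the same edit, reconcile the absolute increase of 24.57 per 1000 with the doubling that actually gives 1835.

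The cost of the first route is recalculation, wording and a less favourable stated power for a doubling. Adding 12-month coded AF incidence from INTEGO as a secondary outcome is optional; it would need a later data extraction but no extra visits. The trial status section says recruitment had not started, so on that account the change could precede enrolment.
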